**Table 11: Summary of Baseline Characteristics (Full Ancillary Analysis Population Completers)**

- repeat of Table 8 for Full Ancillary Analysis population study completers

| Table 12: Summary of Primary Outcome Availability (Full Ancillary Analysis Population) |                 |                            |                                      |                      |                                                 |                      |
|----------------------------------------------------------------------------------------|-----------------|----------------------------|--------------------------------------|----------------------|-------------------------------------------------|----------------------|
|                                                                                        |                 |                            | Required COWS Collected  |                      | Clinician Assessment of Precipitated Withdrawal |                      |
| Site                                                                                   | Number Enrolled | Number Receiving Injection | Number                               | Percent  | Number                                          | Percent  |
| Yale-New Haven Hospital ED                                                             | N               | N                          | N                                    | xx.x%                | N                                               | xx.x%                |
| Highland Hospital ED                                                                   |                 |                            |                                      |                      |                                                 |                      |
| Penn Presbyterian Medical Center ED                                                    |                 |                            |                                      |                      |                                                 |                      |
| Rhode Island Hospital ED                                                               |                 |                            |                                      |                      |                                                 |                      |
| Total                                                                                  |                 |                            |                                      |                      |                                                 |                      |

 Three COWS assessments are required: pre-injection COWS, and two post-injection COWS, one of which is within the last hour.

 The denominator is the number of participants enrolled.

| Table 13: Summary of Primary Outcome Analysis (Primary Ancillary Analysis Population) |                                                                                                      |           |                                      |
|---------------------------------------------------------------------------------------|------------------------------------------------------------------------------------------------------|-----------|--------------------------------------|
| Number Enrolled                                                                       | Primary Outcome Measure                                                                              | N (%)     | 95% Confidence Interval  |
| N                                                                                     | Participant experienced a 5 or greater increase in COWS score within 4 hours of the XR-BUP injection | N (xx.x%) | xx.xx% - xx.xx%                      |
|                                                                                       | Participant transitioned to moderate withdrawal within 4 hours of the XR-BUP injection               | N (xx.x%) | xx.xx% - xx.xx%                      |
|                                                                                       | Participant experienced a precipitated withdrawal within 1 hour of the XR-BUP injection              | N (xx.x%) | xx.xx% - xx.xx%                      |

Missing COWS scores or precipitated withdrawals are imputed as having experienced the event.

 Calculated using the Exact Clopper-Pearson method.

Table 14: Summary of Primary Outcome Analysis (Full Ancillary Analysis Population)

- repeat Table 13 for Full Ancillary Analysis population

**Table 15: Summary of Primary Outcomes by Subgroup (Full Ancillary Analysis Population)**

| Subgroup                | Number
Enrolled | Participant experienced a 5 or greater increase in COWS score within 4 hours of the XR-BUP |                     | Participant transitioned to moderate withdrawal within 4 hours of the XR-BUP injection |                     | Participant experienced a precipitated withdrawal within 1 hour of the XR-BUP injection |                     |
|-------------------------|--------------------|--------------------------------------------------------------------------------------------|---------------------|----------------------------------------------------------------------------------------|---------------------|-----------------------------------------------------------------------------------------|---------------------|
|                         |                    | N (%)                                                                                      | 95% CI  | N (%)                                                                                  | 95% CI  | N (%)                                                                                   | 95% CI  |
| Overall          | N                  | N (xx,x%)                                                                                  | xx.xx% - xx.xx%     | N (xx,x%)                                                                              | xx.xx% - xx.xx%     | N (xx,x%)                                                                               | xx.xx% - xx.xx%     |
| Age              |                    |                                                                                            |                     |                                                                                        |                     |                                                                                         |                     |
| ≤ 35                    | N                  | N (xx,x%)                                                                                  | xx.xx% - xx.xx%     | N (xx,x%)                                                                              | xx.xx% - xx.xx%     | N (xx,x%)                                                                               | xx.xx% - xx.xx%     |
| > 35                    |                    |                                                                                            |                     |                                                                                        |                     |                                                                                         |                     |
| Gender           |                    |                                                                                            |                     |                                                                                        |                     |                                                                                         |                     |
| Male                    | N                  | N (xx,x%)                                                                                  | xx.xx% - xx.xx%     | N (xx,x%)                                                                              | xx.xx% - xx.xx%     | N (xx,x%)                                                                               | xx.xx% - xx.xx%     |
| Female                  |                    |                                                                                            |                     |                                                                                        |                     |                                                                                         |                     |
| Ethnicity        |                    |                                                                                            |                     |                                                                                        |                     |                                                                                         |                     |
| Hispanic                | N                  | N (xx,x%)                                                                                  | xx.xx% - xx.xx%     | N (xx,x%)                                                                              | xx.xx% - xx.xx%     | N (xx,x%)                                                                               | xx.xx% - xx.xx%     |
| Not Hispanic            |                    |                                                                                            |                     |                                                                                        |                     |                                                                                         |                     |
| Race |                    |                                                                                            |                     |                                                                                        |                     |                                                                                         |                     |
| White                   | N                  | N (xx,x%)                                                                                  | xx.xx% - xx.xx%     | N (xx,x%)                                                                              | xx.xx% - xx.xx%     | N (xx,x%)                                                                               | xx.xx% - xx.xx%     |
| Black                   |                    |                                                                                            |                     |                                                                                        |                     |                                                                                         |                     |
| Other                   |                    |                                                                                            |                     |                                                                                        |                     |                                                                                         |                     |

Participants with missing values for COWS scores or precipitated withdrawals are imputed as having experienced the event.

 Confidence interval (CI) calculated using the Exact Clopper-Pearson method.

 Excludes participants who refused to answer or did not know their race.

**Figure 4: Percentage (95% CI) of Participants who Experienced a 5 or Greater Increase in COWS Scores Within 4 Hours of the XR-BUP by Subgroup (Full Ancillary Analysis Population)**

[figure not shown]

Participants with missing values for COWS scores or precipitated withdrawals are imputed as having experienced the event.

 Confidence interval (CI) calculated using the Exact Clopper-Pearson method.

 Excludes participants who refused to answer or did not know their race.

**Figure 5: Percentage (95% CI) of Participants who Transitioned to Moderate Withdrawal Within 4 Hours of the XR-BUP Injection by Subgroup (Full Ancillary Analysis Population)**

Similar to Figure 4.

**Figure 6: Percentage (95% CI) of Participants who Experienced a Precipitated Withdrawal Within 1 Hour of the XR-BUP Injection by Subgroup (Full Ancillary Analysis Population)**

Similar to Figure 4.

**Table 16: Summary of Primary Outcome Supportive Analyses (Full Ancillary Analysis Population)**

| Subgroups                                                       | Level         | Number Enrolled | Participant experienced a greater increase in COWS score within 4 hours of the XR-BUP injection N (%; 95% CI  ) | Participant transitioned to moderate withdrawal within 4 hours of the XR-BUP injection N (%; 95% CI  ) | Participant experienced a precipitated withdrawal within 1 hour of the XR-BUP injection N (%; 95% CI  ) |
|-----------------------------------------------------------------|---------------|-----------------|-----------------------------------------------------------------------------------------------------------------------------|--------------------------------------------------------------------------------------------------------------------|---------------------------------------------------------------------------------------------------------------------|
| Enrolled before/after eligibility criteria changes  | Before        | N               | N (xx.x%, xx.xx% - xx.xx%)                                                                                                  | N (xx.x%, xx.xx% - xx.xx%)                                                                                         | N (xx.x%, xx.xx% - xx.xx%)                                                                                          |
|                                                                 | After         |                 |                                                                                                                             |                                                                                                                    |                                                                                                                     |
| COWS score at baseline                              | 4 – 7         | N               | N (xx.x%, xx.xx% - xx.xx%)                                                                                                  | N (xx.x%, xx.xx% - xx.xx%)                                                                                         | N (xx.x%, xx.xx% - xx.xx%)                                                                                          |
|                                                                 | < 4           |                 |                                                                                                                             |                                                                                                                    |                                                                                                                     |
| Positive for fentanyl at baseline                   | No            | N               | N (xx.x%, xx.xx% - xx.xx%)                                                                                                  | N (xx.x%, xx.xx% - xx.xx%)                                                                                         | N (xx.x%, xx.xx% - xx.xx%)                                                                                          |
|                                                                 | Yes           |                 |                                                                                                                             |                                                                                                                    |                                                                                                                     |
| COWS score at baseline and positive for fentanyl at baseline    | 4 – 7 and no  | N               | N (xx.x%, xx.xx% - xx.xx%)                                                                                                  | N (xx.x%, xx.xx% - xx.xx%)                                                                                         | N (xx.x%, xx.xx% - xx.xx%)                                                                                          |
|                                                                 | 4 – 7 and yes |                 |                                                                                                                             |                                                                                                                    |                                                                                                                     |
|                                                                 | < 4 and no    |                 |                                                                                                                             |                                                                                                                    |                                                                                                                     |
|                                                                 | < 4 and yes   |                 |                                                                                                                             |                                                                                                                    |                                                                                                                     |

Participants with missing values for COWS scores or precipitated withdrawals are imputed as having experienced the event.

 Calculated using the exact Clopper-Pearson method.

 One participant in the Full Ancillary Analysis Population had a missing COWS score at baseline.

 Eligibility criteria were updated with protocol version 4.0. The following changes were made: (i) patients with urines that were only positive for fentanyl on the point of care test strip were eligible if their clinical history and physical exam were consistent with opioid use and they met DSM-5 criteria for moderate to severe OUD; (ii) having an index ED visit due to opioid overdose was no longer considered an exclusion criteria; and (iii) the definition of current enrollment in the exclusion criteria of formal addition treatment was changed from 14 to 7 days.

**Table 17: Summary of Primary Outcome Analysis (Primary Ancillary Analysis Population)**

- repeat Table 16 in the Primary Ancillary Analysis population

| Table 18: Summary of Primary Outcomes: Supportive Analyses, Not Pre-specified (Full Ancillary Analysis Population) |                                                                                                                                                                                         |              |                                            |
|---------------------------------------------------------------------------------------------------------------------------|-----------------------------------------------------------------------------------------------------------------------------------------------------------------------------------------|--------------|--------------------------------------------|
| Number Enrolled                                                                                                    | Outcome Measure                                                                                                                                                                  | N (%) | 95% Confidence Interval |
| N                                                                                                                         | Participant experienced a 5 or greater increase in COWS score within 4 hours of the XR-BUP injection, in the absence of a precipitated withdrawal within 1 hour of the XR-BUP injection | N (xx.x%)    | xx.xx% - xx.xx%                            |
|                                                                                                                           | Participant transitioned to moderate withdrawal within 4 hours of the XR-BUP injection, in the absence of a precipitated withdrawal within 1 hour of the XR-BUP injection               | N (xx.x%)    | xx.xx% - xx.xx%                            |

Participants with missing values for COWS scores or precipitated withdrawals are imputed as having experienced the event.

 Calculated using the Exact Clopper-Pearson method.

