## **3. Participant experienced a precipitated withdrawal within 1 hour of XR-BUP injection**

- Potential precipitated withdrawal events are adjudicated by study consultants and captured on the PWD eCRF as 'Yes' or 'No' at 240 minutes after the XR-BUP injection. If the time listed for this precipitated withdrawal is within 1 hour of the time of XR-BUP injection (including exactly 1 hour), the participant is considered to have experienced this outcome.
- In order for this outcome to be evaluable (i.e., non-missing), the PWD eCRF must be completed with a time of precipitated withdrawal provided one occurred.

For all three outcome measures, if the outcome measure is not evaluable (i.e., missing), the worst-case scenario will be imputed for that outcome measure where the participant is assumed to have experienced the outcome measure.

The *a priori* conditions on these outcomes in the Primary Ancillary Analysis population to inform expanding enrollment in the RCT component are:

- <20% of participants will experience a 5 or greater increase in COWS score within 4 hours of injection
- <10% of participants will transition to moderate withdrawal (COWS score 13 to 24, inclusive) within 4 hours of injection
- <10% of participants will experience precipitated withdrawal within 1 hour of injection

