#### **7.1.5 Additional Outcome Measures**

Two additional outcome measures, not pre-specified in the protocol, will be computed:

1. Participant experienced a 5 or greater increase in COWS score within 4 hours of the XR-BUP injection, in the absence of a precipitated withdrawal within 1 hour of the XR-BUP injection.
2. Participant transitioned to moderate withdrawal within 4 hours of the XR-BUP injection, in the absence of a precipitated withdrawal within 1 hour of the XR-BUP injection.

These outcomes will be analyzed in the same manner as the primary outcome. Tables will be generated for the Full Ancillary Analysis and Primary Ancillary Analysis populations.

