**Table 19: Summary of Primary Outcomes: Supportive Analyses, Not Pre-specified (Primary Ancillary Analysis Population)**

- repeat Table 18 in the Primary Ancillary Analysis population

| Table 20: Summary of Safety Events (Safety Population) |                        |                           |                                                                               |                                                                              |                                      |                      |                       |                  |      |
|--------------------------------------------------------|------------------------|---------------------------|-------------------------------------------------------------------------------|------------------------------------------------------------------------------|--------------------------------------|----------------------|-----------------------|------------------|------|
| Site                                                   | Number of Participants |                           |                                                                               |                                                                              |                                      |                      |                       | Number of Events |      |
|                                                        | Enrolled               | Received XR-BUP Injection | Experienced a 5 or greater increase in COWS score within 4 hours of injection | Transitioned to moderate withdrawal (COWS 13-24) within 4 hours of injection | Precipitated Withdrawal  | With at least One AE | With at least One SAE | AEs              | SAEs |
| Yale-New Haven Hospital ED                             | N                      | N                         | N (xx.x%)                                                                     | N (xx.x%)                                                                    | N (xx.x%)                            | N (xx.x%)            | N (xx.x%)             | N                | N    |
| Highland Hospital ED                                   |                        |                           |                                                                               |                                                                              |                                      |                      |                       |                  |      |

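### The missing-data footnote to SAP Tables 18 and 19 misclassifies some participants, because precipitated withdrawal enters those outcomes negated

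*Combined protocol and SAP*

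**What the plan says.** SAP 7.1.1 defines three primary outcomes for the ancillary component: a COWS rise of 5 or more within 4 hours, a transition to moderate withdrawal within 4 hours, and PW within 1 hour. Each has its own evaluability rule. For PW, "the PWD eCRF must be completed with a time of precipitated withdrawal provided one occurred". When one of the three is not evaluable, "the worst-case scenario will be imputed for that outcome measure where the participant is assumed to have experienced the outcome measure".

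SAP 7.1.5 then adds two outcomes that the protocol did not pre-specify. Each takes one of the COWS events and requires that it happen "in the absence of a precipitated withdrawal within 1 hour of the XR-BUP injection". On method the section says only: "These outcomes will be analyzed in the same manner as the primary outcome". It gives no evaluability rule for the combined outcomes.

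The shells in SAP 17.1.1 report these outcomes in Table 18 (Full Ancillary Analysis population) and Table 19 (instruction: "repeat Table 18 in the Primary Ancillary Analysis population"). The Table 18 footnote reads: "Participants with missing values for COWS scores or precipitated withdrawals are imputed as having experienced the event". The same sentence stands under Tables 15 and 16, where PW has its own column.

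**The concern.** In Tables 15 and 16, PW is an adverse outcome in its own right, so filling in a missing value as yes is the unfavourable choice. In Tables 18 and 19 the outcome is a COWS event with PW absent. Filling in PW as yes now removes the participant from the event count. The footnote was carried over without allowing for this change of direction. It also does not say whether the event it imputes is the component or the combined outcome.

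These tables exist to show how much withdrawal occurred apart from PW. If the footnote is programmed as written, participants with incomplete data can be put on the wrong side of that split, under a rule that SAP 7.1.4 describes as worst case.

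Incomplete data are foreseeable. Both ancillary analysis populations are defined by consent (SAP 3.1.1.2 and 3.1.1.3), so a participant who was enrolled but not injected stays in the denominator with no post-injection COWS. The Table 12 shell counts enrolled and injected participants separately.

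**Working it through.** **The plan's own figure.** The tables use exact (Clopper-Pearson) 95% intervals. With x events among n, the lower limit is the 0.025 quantile of Beta(x, n−x+1) and the upper limit is the 0.975 quantile of Beta(x+1, n−x). SAP 10.1 gives interval widths at n=75 for proportions 0.01, 0.05, 0.10, 0.15, 0.20, 0.25 and 0.30. Setting x = 75p reproduces them within rounding: 0.0664, 0.1134, 0.1485, 0.1732, 0.1918, 0.2062 and 0.2173, against the stated 0.066, 0.113, 0.148, 0.173, 0.192, 0.206 and 0.217.

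**Inputs for the classification check.** The outcomes are the two in SAP 7.1.5, both with PW limited to the first hour: a COWS rise of 5 or more without PW, and "Participant transitioned to moderate withdrawal within 4 hours of the XR-BUP injection, in the absence of a precipitated withdrawal within 1 hour". Write the outcome as E = (COWS event) and not (PW within 1 hour). COWS counts as missing when it is not evaluable under SAP 7.1.1. Three rules are compared:

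- A: each missing component is set to yes, and E is then computed.
- B: E is set to yes whenever either component is missing.
- C: E is set to yes only when the observed data leave it undetermined, which is the logical worst case.

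| COWS event | PW within 1 h | E can be | A | B | C |
|---|---|---|---|---|---|
| yes | missing | yes or no | no | yes | yes |
| no | missing | no only | no | yes | no |
| missing | yes | no only | no | yes | no |
| missing | no | yes or no | yes | yes | yes |
| missing | missing | yes or no | no | yes | yes |

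With both components observed, the three rules agree. In the five cells with missing data, A departs from C in two: it drops an observed rise when PW is missing, and it scores a participant missing both as a non-event. B also departs from C in two: it creates events in both cells where the observed data allow only a non-event.

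**Size.** One participant is worth 1/75 = 1.3 percentage points, or 1/100 = 1.0 point at the enlarged sample of about 100. The documents give no count of missing PW forms, so the following counts are assumed. Take 6 fully observed events plus one participant in each of the four cells where A or B departs from C:

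| n | A | B | C |
|---|---|---|---|
| 75 | 6 (8.0%, CI 3.0–16.6) | 10 (13.3%, CI 6.6–23.2) | 8 (10.7%, CI 4.7–19.9) |
| 100 | 6 (6.0%, CI 2.2–12.6) | 10 (10.0%, CI 4.9–17.6) | 8 (8.0%, CI 3.5–15.2) |

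For C, 6 + 1 (rise, PW missing) + 1 (both missing) = 8. For B, 6 + 4 = 10. If no participant falls in those four cells, all three rules give 6.

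**Documented missingness.** The only case on record is one participant with no baseline COWS score (footnote to Table 16). If COWS is not evaluable for that participant and PW was recorded as absent, all three rules score an event, so the choice of rule makes no difference.

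**The case against.** The strongest reply is that the body text governs and the footnote is shorthand in a table shell. SAP 7.1.1 imputes only when the outcome measure is not evaluable, and only for that measure. It also already treats limited COWS data as sufficient when they show an event. Carried over by 7.1.5, this can be read as imputing only when the combined outcome is undetermined, which is rule C. That reading is sound and available. But the footnote is triggered by any missing COWS or PW value, and no evaluability rule is written for these two outcomes, so a programmer would have to supply rule C unaided.

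It is also fair to say that missingness would be visible. Table 12 reports availability of COWS and PW separately, and Listing 1 shows the components by participant. That lets a reader notice the problem but does not correct the tables.

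Four stronger inferences are tempting, and the documents do not support them:

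- **That the rule makes XR-BUP look better.** This holds only for component-level imputation (A). Imputing the combined outcome (B) errs by over-counting.
- **That every participant without a PW form is reallocated.** Under A, a participant with an evaluable COWS series and no rise is a non-event either way.
- **That counting a participant missing both as PW in Table 13 and as a rise without PW in Table 19 is an error.** Separate worst-case bounds need not be jointly attainable, and the correct worst case (C) has the same feature.
- **That the expansion of the RCT is in doubt.** The 10% and 20% conditions in SAP 7.1.1 and 11.2 apply to the three primary outcomes, where the rule is a true worst case. No limit applies to Tables 18 and 19.

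**Conclusion.** The footnote to Tables 18 and 19 is a faulty stated rule for outcomes in which PW is negated. Component-level use is not worst case in two of the five missing-data cells. Use on the combined outcome whenever either component is missing overrides observed data in two of the five.

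The effect is 1.3 percentage points per affected participant at n=75 and 1.0 at n=100. The number affected is unknown and may be zero. The conclusion rests on the wording of the footnote and on the absence of an evaluability rule in 7.1.5; if the analyst already applies rule C, the numbers are right and only the text needs correcting.

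Severity is minor. The outcomes are supportive and not pre-specified, and no decision is tied to them.

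**What to change.** In SAP 7.1.5 and in the footnotes to Tables 18 and 19, score each combined outcome directly instead of reusing the PW value imputed for Table 13:

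- No, if an evaluable COWS series shows no rise (or no transition), or if PW within 1 hour is observed.
- Yes, if the rise (or transition) is observed and PW is observed absent or missing.
- Yes, as the worst case, if COWS is not evaluable and PW is observed absent or missing.

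Report the number of participants imputed beneath each table.

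The cost is one paragraph and a few lines of code, with no new data. The reported rate may change slightly, in a direction that depends on which reading would otherwise have been programmed.
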